### Research participants

*Adolescent participants* for Phase 1 (formative research) will be recruited from among HIV-positive patients aged 12–17 years who receive ART at NHP, along with their primary caregivers. All of these patients were perinatally infected. Adolescent participants for Phase 2 (RCT) will be recruited from the same NHP population. To be enrolled in either phase, adolescents must be on ART, in care at NHP (or graduated from NHP care in the case of older youth at adult OPCs), agree to follow study procedures, provide informed assent, and have their caregiver provide written informed consent. For the RCT, additional inclusion criteria will apply; participants in Phase 1 activities will be eligible to participate in the Phase 2 RCT. Adolescents must also expect to remain in care at the NHP for seven months minimum and be identified as having adherence challenges, defined by: detectable VL, CD4 < 700 in the last six months, or decline in CD4 in the last six months. Adolescents who are aged < 12 years or > 18 years, live outside the clinic catchment area, decline to provide informed assent, have a caregiver who declines to provide consent, or have a mental health condition sufficiently serious that they cannot understand informed assent, including the voluntary nature of participation, will be excluded.

*Adolescent participants* aged ≥ 18 years for Phase 1 (formative research) will be recruited from among HIV+ patients aged 18–21 years who have transitioned to care at OPCs in Hanoi. *Caregiver participants* for Phase 1 (formative research) must be identified as the child’s primary caregiver and will be recruited along with the adolescent patients at NHP selected for the IDIs or FGDs. *Clinician participants* from the Infectious Disease Clinic at NHP will be recruited for participation in Phase 1 (formative research) and all clinicians there will be eligible.

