### RCT data collection procedures

Once enrolled, RCT participants will provide study data as follows:*Sociodemographic data and SDT constructs*: upon enrollment, all participants will complete a baseline survey with the site coordinator which will cover: age; gender; ethnicity; education; school-going behaviors; family routines; scales for each of the SDT constructs; self-efficacy; stigma; a child depression index; and a strengths and difficulties index.*Continuous adherence data in Months 1–7*: data on WPC openings will be transmitted continuously via 3G cellular network to a central server, which will automatically download data to a password-protected web-based database that investigators can access as needed for analysis. This system will provide adherence data for each participant. We will also collect data on the frequency of reminder messages sent to each participant by type of reminder, for intervention participants only.*Continuous data on signal lapses*: during Month 1, we will investigate all WPC signal lapses lasting ≥ 48 h by phone call to the participant and determine whether a lapse was due to technical failure (battery failure, forwarder malfunction) or behavioral cause (missed dose, intentional non-use).*Device utilization questionnaire*: we will administer a survey on adolescents’ experience using the WPC at the Month 1 visit for all participants.*Monthly check-in questionnaire*: a brief questionnaire will be administered to all participants to collect data on: whether adherence counseling occurred (yes/no); who was responsible for WPC management; and the occurrence of any major life events (including status disclosure).*Month 7 follow-up questionnaire*: a final survey will be administered to all participants at the end of the intervention period, similar to that completed at baseline, with the addition of a brief quantitative and open-ended questionnaire asking about experience with the WPC, including convenience of use, storage, and potential stigma/loss of confidentiality.*Biological samples*: all participants will provide blood samples for CD4 count and VL tests at Month 1 (pre-randomization) and Month 7 (post-intervention period). Standard of care in Vietnam is CD4 count testing every three months and VL testing every six months free of charge to patients, but VL tests are rarely done due to cost. We will try to time enrollment to align with patients’ blood draw schedule such that, in general, no additional blood draws will be necessary for VL or CD4 tests, but some patients may be enrolled at a time when they are not due for a regular CD4 test; these patients will require an extra blood draw for the study at enrollment. All samples will be identified only by the patient’s study ID to ensure confidentiality. Data will be provided to the clinic for addition to participants’ charts in order to inform treatment. All extra testing costs will be paid for by the research project budget.

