### Analytic approach (Specific Aim 4)

In accordance with this study aim (to generate preliminary data regarding the efficacy of the real-time feedback package on adherence, CD4 count, and VL), this analysis will be non-confirmatory. We will assess differences between intervention and control in post-intervention proportions achieving optimal adherence, mean adherence, mean CD4, and proportions achieving UDVL, also stratified by optimal or sub-optimal adherence in the pre-randomization period. We will report the following comprehensive set of outcomes, including measures of effect, test statistics, and significance:

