#### Adherence

Mean adherence, comparing Month 7 to Month 0, and intervention versus control, and in each month of the intervention;% ≥ 95% adherence comparing Month 7 to Month 0, and intervention versus control, and in each month of the intervention.

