### General approach

We will calculate descriptive statistics for all study variables (means, ranges, standard deviations, percent data missing, and frequencies, percentages for categorical variables). For adherence, a non-opening for a scheduled dose will be considered a non-adherent dose. Repeated openings within the same scheduled dose time will be excluded. Outcomes will not be imputed for patients who drop out. Patients who drop out before randomization will be excluded in experimental analyses. Sociodemographic and clinical characteristics from baseline will be compared between those randomized and those not randomized to assess representativeness of the final analytic sample, using Cochran Mantel–Haenszel χ^2^ tests for categorical variables and Student’s *t* tests for continuous variables. After randomization, we will compare dropout rates and characteristics of patients who drop out between study arms to assess potential for bias using the same statistical tests. All randomized participants will be included in analyses. We will perform both intention-to-treat (ITT) and per-protocol analyses.

For the main dichotomous outcome (% ≥ 95% adherence after the intervention [Month 7]), risk differences and 95% confidence intervals will be calculated. UDVL will be similarly treated as a secondary dichotomous outcome. We will then construct multivariate regression models to adjust for key baseline variables such as gender, using high adherence as the outcome, and intervention group as the primary predictor. Other variables found to be significantly associated with high adherence in bivariate logistic models will be added using forward-stepwise and forced entry techniques. We will also conduct stratified analyses based on gender and other attributes, although we may only have statistical power to detect trends. For continuous outcomes (change in adherence and CD4 count), we will use paired t-tests and General Linear Models to test for differences before and after intervention, then use similar multivariate approaches as described above. To examine interrelationships among adherence and the constructs of our theoretical model, stigma, and other psychosocial measures, we will generate bivariate Pearson correlations and conduct exploratory path analysis.

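### For mean adherence and CD4 the plan names before/after tests and fixes no baseline-adjusted between-arm estimate; separately, the Month 0 label needs reconciling

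*Protocol article*

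**What the plan says.** General approach treats the two kinds of outcome differently. The main dichotomous outcome (at least 95% adherence at Month 7) gets a risk difference with a 95% confidence interval. For the continuous outcomes, change in adherence and CD4 count, "we will use paired t-tests and General Linear Models to test for differences before and after intervention", and the sentence ends "then use similar multivariate approaches as described above". The models it points back to are built "using high adherence as the outcome, and intervention group as the primary predictor". They adjust for baseline variables such as gender and add others on the strength of bivariate significance.

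Other sections state the contrasts. Analytic approach (Specific Aim 4) has "We will assess differences between intervention and control in post-intervention proportions achieving optimal adherence, mean adherence, mean CD4, and proportions achieving UDVL". The end of that sentence extends the same between-arm comparison to the baseline strata: "also stratified by optimal or sub-optimal adherence in the pre-randomization period". The Adherence list has "Mean adherence, comparing Month 7 to Month 0, and intervention versus control". Clinical markers lists change in CD4 from baseline to endline and between arms. Specific Aim 4 also declares the analysis non-confirmatory.

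On timing, RCT data collection procedures has "Continuous adherence data in Months 1–7", with blood drawn at Month 1 before randomisation and again at Month 7. The pre-intervention section calls the monitoring month Month 1 and forms the randomisation strata from that month's adherence. Eligibility (Research participants) requires a detectable viral load, CD4 below 700, "or decline in CD4 in the last six months".

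**The concern.** General approach is where tests are assigned to outcomes. For the continuous outcomes, the stated purpose of both named methods is a before/after difference. A paired t-test answers whether one group changed, not whether the intervention changed it. Anything that moves both arms (wearing-off of novelty, clinic trends, regression to the mean) enters the result in full. The plan also promises significance results for the whole outcome list, so within-arm p-values are likely to appear next to the randomised contrasts.

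At stake is how mean adherence and CD4 are read when the team decides, as Dissemination foresees, whether to plan a larger effectiveness study. A second cost is precision: the Month 1 value and the stratum are collected for everyone, but the article does not commit to using them in the between-arm estimate.

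**Working it through.** **1. The plan's own figure.** The only power statement (Sample size and power considerations) is for the dichotomous outcome: 40 per arm, two-sided 0.05, 80% power, 29 points. Take 51.8% against 51.8 + 29 = 80.8%, so the mean proportion is 0.663.

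n = [1.96·√(2·0.663·0.337) + 0.842·√(0.518·0.482 + 0.808·0.192)]² / 0.29² = (1.310 + 0.535)² / 0.0841 ≈ 40.5, so 41 per arm. Power at 40 is 79.5%. The figure reproduces within rounding and does not depend on the test disputed here. No power is stated for the continuous outcomes.

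**2. What each test targets.** Let T be a trend common to both arms, R regression to the mean, and E the intervention effect. Expected mean change is T + R in control and T + R + E in intervention. A paired test in the intervention arm tests T + R + E = 0. The between-arm comparison tests (T + R + E) − (T + R) = E. Only the second isolates E.

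**3. How large R can be.** Assume normal data with baseline–endline correlation ρ and a group made up of the lowest fraction q on the baseline value itself. In SD units of the unselected population, R = (1 − ρ)·φ(c)/q with c = Φ⁻¹(q). The factor φ(c)/q is 0.798 for q = 0.5 and 0.497 for q = 0.7. A simulation with no intervention effect (3,000 replicates) gives the rejection rates. Neither ρ nor q is in the document.

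| ρ | q | R (formula) | paired, n = 40 | between-arm, 40 per arm | paired, n = 20 | between-arm, 20 per arm |
|---|---|---|---|---|---|---|
| 0.5 | 0.5 | 0.40 | 77.1% | 5.3% | 43.7% | 4.9% |
| 0.5 | 0.7 | 0.25 | 38.3% | 5.4% | 20.1% | 5.8% |
| 0.7 | 0.5 | 0.24 | 48.9% | 4.5% | 27.9% | 5.4% |
| 0.7 | 0.7 | 0.15 | 22.7% | 5.4% | 13.0% | 5.4% |
| 0.9 | 0.5 | 0.08 | 19.9% | 4.6% | 12.4% | 4.7% |
| 0.9 | 0.7 | 0.05 | 10.4% | 5.2% | 7.4% | 5.4% |

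If selection is instead on a separate earlier measurement, with all three measurements equally correlated, the paired test rejects in 4.2% to 5.7%.

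**4. Where these figures could apply.**
- Adherence, whole arm: entry is not on container-measured adherence, so the table does not describe it. A common trend T remains possible.
- Adherence, below-95% stratum: the stratifying value is also the before value, so R is present in any within-arm reading there.
- CD4: R of this kind arises if the qualifying draw also serves as the Month 1 baseline. The article says enrolment will be timed to routine draws where possible, which allows this but does not establish it.

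**5. Precision of the between-arm estimate.** With equal variances, the variance relative to baseline adjustment is 2/(1 + ρ) for change scores and 1/(1 − ρ²) for Month 7 values alone.

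| ρ | change score | Month 7 only |
|---|---|---|
| 0.5 | 2/1.5 = 1.33 | 1/0.75 = 1.33 |
| 0.7 | 2/1.7 = 1.18 | 1/0.51 = 1.96 |
| 0.9 | 2/1.9 = 1.05 | 1/0.19 = 5.26 |

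Under this model baseline adjustment is never worse, but the size of the gain depends on a correlation that is not given.

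**6. Month labels.** The Adherence list measures change from Month 0. The data collection section records adherence in Months 1 to 7, and the pre-intervention section labels the baseline month Month 1. The text does not define Month 0. CD4 is unaffected, since its baseline is dated Month 1.

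**The case against.** The strongest reply is that the randomised comparison is already planned. The sentence on continuous outcomes names General Linear Models as well as paired tests and goes on to models with arm as the primary predictor. Specific Aim 4 and both outcome lists state intervention-versus-control comparisons. Regression to the mean acts alike on both randomised arms and does not bias those contrasts. Covariate detail may sit in the analysis plan, which is not shown. All of this stands. It rules out the reading that the continuous outcomes are tested only by before/after comparison.

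A reader might also infer that paired tests will be run inside the baseline-adherence strata, where R is largest. The document does not say so: the stratified analysis under Specific Aim 4 is a between-arm, post-intervention comparison. In the optimal stratum regression to the mean would in any case produce a fall, which could not pass for benefit. The n = 20 columns above therefore illustrate a mechanism and are not the error rate of a stated analysis.

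Nor does selecting on low or falling CD4 by itself show that CD4 change will be inflated. Eligibility uses clinic history, and patients not due a test get an extra draw at enrolment. With a separate qualifying measurement the simulated paired test kept its nominal level.

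What the reply leaves untouched is narrower. The purpose stated for the named tests is a before/after difference. The models referred to name neither the Month 1 value nor the stratum, and they add covariates by significance. No between-arm estimate with an interval is fixed for mean adherence or CD4, as one is for the dichotomous outcome.

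**Conclusion.** The point holds as a limited one. For change in adherence and CD4 the article assigns before/after tests, one of which ignores randomisation, and it fixes no baseline-adjusted between-arm estimate. The between-arm contrasts are listed and remain valid, so this is a badly specified test of effect rather than a missing randomised comparison.

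No size can be fixed from the document. The false-positive rates of 10% to 77% at n = 40 rest on assumed correlations of 0.5 to 0.9 and on entry limited to the lowest 50% to 70% of the baseline value itself. They fall to about 5% if selection uses a separate measurement. The precision gain rests on the same unknown correlation.

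The consequence is bounded: the main outcome is dichotomous and analysed by between-arm risk differences, and the efficacy analysis is declared non-confirmatory.

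Month 0 is a separate labelling inconsistency. A reader might take it to mean that baseline adherence is never recorded, or that the label is a source of regression to the mean. Neither follows: it may simply be another name for the pre-intervention month, and the schedule and study-profile figures are not shown.

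**What to change.** - Make the test of effect for mean adherence and for CD4 a linear model of the Month 7 value on arm, the Month 1 value of the same measure and the randomisation stratum. Report the adjusted between-arm difference with a 95% confidence interval.
- Present within-arm paired changes as description only, without using their p-values as evidence of efficacy.
- Use one label for the adherence baseline: either replace Month 0 by Month 1 (pre-randomisation), or define Month 0 explicitly as that month.

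The cost is wording. Arm, stratum and both Month 1 values are already collected, and neither the sample size nor the main dichotomous analysis changes. If the analysis plan already specifies such a model, aligning the article's sentence with it is enough.

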### Sample size and power considerations

The formative component in Phase 1 will include: IDIs with adolescent/caregiver dyads (20 dyads, for a total of 40 IDIs); one FGD with 8–10 clinicians; one FGD with 8–10 caregivers; up to six FGDs with adolescent patients (three with girls, three with boys, with 8–10 participants each; maximum 60 total participants); 20 IDIs with older adolescents aged ≥ 18 years receiving care at adult OPCs (10 with young women, 10 with young men). Total maximum qualitative participants will be 140: 40 IDIs with NHP adolescent patients/caregivers; 10 clinicians in FGD, 10 caregivers in FGD, 60 FGD participants aged 12–15 years; 20 IDI participants aged ≥ 18 years. These numbers are adequate to elicit a range of experiences of youth, their caregivers, and clinicians.

We have powered the RCT in Phase 2 to be able to detect meaningful changes in optimal adherence. We will recruit 80 adolescent patients, 40 per study arm, which will provide a minimum of 80% power at a two-sided alpha of *p* = 0.05 to detect specified differences in adherence between the two arms after intervention. Our estimates of outcome differences are based on our findings from our earlier CATS study with Chinese adults, in which we found that proportions achieving ≥ 95% adherence were 87.3% versus 51.8%, in intervention versus control patients after six months of the intervention [43]. We will have a minimum of 80% power to detect down to a 29 percentage-point difference in proportions achieving ≥ 95% adherence between arms after the intervention.

### Efforts to protect against standard risks of bias in unmasked trials

Although the nature of our intervention does not allow for blinding of trial participants or care providers, we have put into place the following protections. To protect against *selection bias*, we are using a stratified block randomization technique (as noted above) including allocation concealment via sequentially numbered, sealed, opaque envelopes. Due to the nature of the intervention, which involves clinician counseling, it is not possible to employ blinding, so our findings are at some risk of *performance bias*, although we are providing extensive training to care providers and study personnel to encourage them to standardize their interactions with all participants, with the sole exception of the intervention counseling component.

Our primary adherence outcomes for both intervention and control participants are measured using an electronic adherence monitoring device, an objective measure of adherence that does not involve human knowledge of allocation. Lab personnel who conduct CD4 and viral load processing are also not aware of allocation and have no direct contact with study personnel or participants. We believe that *detection bias* is therefore not of major concern to the study. As for *attrition bias*, we do not expect a great degree of loss to follow-up, withdrawals, or missingness for measures in this short, intensive study, but in addition to comparing background characteristics of those who withdraw or are lost to follow-up, to quantify the impact of missingness that may be non-random and possibly related to (for example) depression (non-ignorable missingness), we will conduct sensitivity analysis using ISNI methods. As noted above, we will conduct ITT and per-protocol analyses for comparison but will prioritize ITT in our reporting of findings.

### Dissemination

We have registered the trial in ClinicalTrials.gov. After data collection is complete, and within two years of completion, we will report results in ClinicalTrials.gov, including a flow chart of study recruitment and dropout, demographic and baseline characteristics of participants, primary and secondary outcomes (adherence, CD4, viral load), statistical test results, and AE information if applicable. After complying with NIH reporting requirements in ClinicalTrials.gov, we will undertake multi-faceted dissemination to make results available to a range of stakeholder audiences, including: (1) meetings in Vietnam with public health officials at all levels, interested patients, and the HIV community; (2) peer-reviewed publications in HIV, social science, and policy and health systems journals; and (3) presentations at national and international conferences, including the International Association of Providers of AIDS Care (IAPAC)’s annual International Adherence Conference. In the preparation of abstracts and publications, we will follow the criteria for authorship recommended by the International Committee of Medical Journal Editors (ICMJE); we do not intend to employ professional writers. If findings indicate, we will work with partners in Vietnam to plan a larger effectiveness study.

### Study principles

The protocol follows the *Standard Protocol Items: Recommendations for Interventional Trials* (SPIRIT) 2013 checklist (Additional file 1), although the reporting of the study’s findings will follow the *Consolidated Standards of Reporting Trials* (CONSORT) guidelines, using the extension for non-pharmacological trials [58].

## Operational issues and discussion

In addition to enhancing understanding of the issues adolescent patients face in order to better tailor support strategies for ART adherence, SAAV is designed to add to our understanding of the feasibility and effectiveness of wireless technology to improve adherence and viral suppression. At the time of submission of this protocol, the team was completing analysis of the Phase 1 qualitative data and enrolling patients for the RCT. During the preparatory period, the team encountered several issues that bear on the conduct of the study and which may be informative to other researchers involved in similar work with adolescents.*Challenges of interviewing adolescents with caregiver present*. We had hoped to interview adolescents (both for the IDIs in the formative phase and the RCT) separately from their caregivers so that youth could be more comfortable in expressing themselves freely with study staff, but in the formative phase, we have encountered the situation that some caregivers prefer to stay in the interview room with their child. We realize that the study team cannot insist on separation, but we believe that some interview and survey data may be affected by a child’s eagerness to please a caregiver (who is present). For the RCT, the study team has devised several strategies to encourage (though never force) caregivers to wait outside the interview room. In all cases, we are documenting whether the caregiver is present for each study activity, in addition to noting how the child and caregiver related in cases when both were present.*Reticence of many adolescents in formative phase*. We discovered that many of the adolescents in the IDIs were reluctant to talk in much detail about their medication-taking behavior, whether a caregiver was present or not. This finding is similar to our experience with adolescents of similar age in China [63]. Our local interviewers devised a series of icebreakers and other games to try to put the adolescents at ease, which has seemed to elicit some additional participation. Exploring adolescents’ general adherence challenges via peer engagement in a FGD format might be another beneficial strategy, perhaps with multiple meetings which could foster trust with facilitators and among participants.*Increasing independence of older adolescents*. We are learning that the increasing independence of older youth in our study population has very real implications for the conduct of the research study. Many of the older adolescent participants (aged 15–17 years) regularly travel to the clinic on their own, which is less costly for the family, but makes it challenging to obtain caregiver consent and therefore to enroll these older youth in study activities. We recently obtained IRB approval to obtain verbal consent from caregivers by phone which we expect to facilitate RCT recruitment.*WPC issues*. While many details had been worked out with the WPC vendor in advance and specified in the contract, additional features and services were requested during the preparatory period related to the use of Vietnamese language messages and specifics of the adherence report used in monthly counseling. These issues were resolved after discussion with the vendor and consultation with our local implementing partners who are experienced in using Vietnamese language with wireless technologies. Researchers should recognize that some logistics and technical details of any technology may be complex when used in global settings; teams should plan to allocate time for working out such matters whenever partnering with any vendor. Our team has had similar experiences with prior technology vendors.*Identification of adolescents at high risk of low adherence*. The team is fully cognizant of the importance of using systematic criteria for identifying adolescents at risk of low adherence as eligible for the RCT. Despite limited preliminary VL data available to the team during the design phase of the study, during the set-up period, we learned that standard of care annual VLs are rarely obtained in northern Vietnam due to cost, so we relied on recent CD4 history (past three and six months) as the main proxies for low adherence risk. Although this not ideal, we were able to adjust the project budget in order to pay for baseline VL tests for all RCT participants which will help to contextualize our adherence findings. Similar future studies should anticipate such issues and include ample funding for dedicated lab testing.*Incorporation into study of older adolescents who have already transitioned to adult care*. Those adolescents who have already transitioned to adult OPC care (aged 18–21 years) likely also experienced adherence challenges and perhaps even greater challenges than those of the NHP age group who are still in pediatric care. These youth are difficult to track in Vietnam, however, due in large part to frequent switching of cell phone numbers related to cell provider promotions. Although this was not explicitly part of our original study objectives, we thought it important to take advantage of our opportunity partnering with the NHP clinic to track some older adolescents who have recently graduated to adult care in order to learn about their experiences. We were able to modify the protocol to include additional IDIs with these older youth in the formative phase via a protocol amendment. We expect that findings from these interviews will provide valuable insight into the pediatric/adolescent HIV care continuum at the critical point of the transition to adult care.

Our experience to date implementing the initial components of the SAAV study highlights the challenges in conducting research in this population of adolescences, as well as the advantages of working closely with local partners to better understand treatment and care issues and respond quickly in terms of data collection modifications. If our hypotheses prove correct, we will advance learning in how to utilize powerful wireless technologies to help adolescent ART patients improve their medication-taking behavior as they approach care transition, with possible relevance for youth with other chronic diseases.

